#### Stage of dementia

To assess the stage of dementia of participants, the Dutch version of the global deterioration scale was used [59]. This classification scale indicates the severity of the dementia from pre-dementia stages (1 to 3) to profound (stage 7).

#### Comorbidity

Comorbid conditions are extracted from the medical status and categorized based on the Dutch translation of the Long-Term Care Facility Resident Assessment Instrument (RAI), section I. This section (disease diagnoses) includes the following categories: 1) *endocrine/metabolic/nutritional*, i.e. diabetes mellitus, hyperthyroidism and hypothyroidism, 2) *heart/circulation*, i.e. arteriosclerotic heart disease, cardiac dysrhythmia, congestive heart failure, deep vein thrombosis, hypertension, hypotension, peripheral vascular disease and other cardiovascular disease, 3) *musculoskeletal*, i.e. arthritis, hip fracture, missing limb (e.g. amputation), osteoporosis and pathological bone fracture, 4) *neurological*, i.e. AD, aphasia, cerebral palsy, cerebrovascular accident, dementia other than AD, hemiplegic/hemi paresis, paraplegia, multiple sclerosis, Parkinson's disease, seizure disorder, transient ischemia attack, traumatic brain injury and quadriplegia, 5) *sensory*, i.e. cataracts, diabetic retinopathy, glaucoma and macular degeneration, 6) *psychiatric/mood*, i.e. anxiety disorder, depression, manic depression (bipolar disorder) and schizophrenia, 7) *pulmonary*, i.e. asthma and emphysema/chronic obstructive pulmonary disease, 8) *other*, i.e. allergies, anaemia, cancer and renal failure.

#### Medication

Medication use is coded according to the Dutch Pharmacotherapeutic Compass and is ranged by the following groups: 1) sedatives, 2) antipsychotics, 3) antidepressants, 4) pychotropics (central nervous system (CNS)), 5) neurological (CNS), 6) anaesthetics and muscle relaxing, 7) blood, 8) cardiovascular, 9) gastrointestinal tract, 10) respiratory tract, 11) kidneys and urinary tract, 12) genital tract, 13) dermatology, 14) otolaryngology, 15) ophthalmologic, 16) infectious diseases, 17) hormones and bone metabolism, 18) corticosteroids nonsteroidal anti-inflammatory drugs (NSAID), 19) corticosteroids nonNSAID, 20) analgesics, antirheumatic drugs and gout agents, 21) vitamins and minerals, 22) malignancies, 23) infectious diseases, 24) various preparations, 25) dentistry, 26) opioids.

### Assessment of physical functioning

For all tests of physical functioning, participants wear their regular footwear and are permitted to use their regular walking aid. As encouragement has been shown to improve performance [60], standardized encouragements will be provided regularly. All tasks are explained and demonstrated to the participants before testing. No practice trials are included. Participants perform the tests under continuous supervision of the researcher to prevent the participants forgetting what they have to do during the tests.

#### Blood pressure

Systolic blood pressure (SBP) and diastolic blood pressure (DBP) are measured on the left arm in millimeters of mercury (mmHg) with an ambulatory blood pressure monitoring device (model 90207, SpaceLabs Medical Inc., Redmond, Washington, USA) while participants are sitting quietly in a chair for at least 5 minutes [61]. This device is automated, lightweight, calibrated and validated [62]. Observers do not wear a white-coat to prevent higher blood pressure measurements due to a white-coat effect and multiple cuff bladders are used to measure blood pressure with a cuff bladder that encircles at least 80% of the arm [61]. In particular, blood pressure of participants with hypertension, i.e. a higher SBP than 160 mmHg and/or a higher DBP than 100 mmHg is expected to decrease during treatment [63]. The SBP and DBP reduction represents the clinical effectiveness of the treatment [64].

#### Six minute walk test (6MWT)

The 6MWT can be used reliably in the assessment of functional endurance ambulation in persons with acquired brain injury [65]. During the performance of the 6MWT, participants are instructed to cover as much distance as possible during 6 minutes with the opportunity to stop and rest if necessary [66]. Participants have to walk around a pre-measured, unobstructed 10 by 1 meter rectangular circuit having semi-circular ends with 0.5 meter radii marked out with plastic cones to prevent participants having to walk at sharp angles. One full round covers 26.3 meters walking. The total walking distance by each participant will be measured to the nearest meter. To estimate the effort of participants during the 6MWT the increase in heart rate will be determined (see heart rate) [67].

#### Heart rate

Heart rate at rest is simultaneously measured with blood pressure. This blood pressure device (see blood pressure) also measures heart rate in beats per minute. In addition, heart rate is measured with a pulse oximeter (CMS 60C TFT color Pulse oximeter) before and directly after the 6MWT for 2 minutes. The faster the heart rate recovers within 1 minute after the 6MWT the healthier the heart; a slower heart rate recovery is associated with more severe coronary artery disease [68].

#### Oxygen saturation

Arterial oxygen saturation is measured before and directly after the 6MWT to determine dyspnea [69]. This is measured with the same pulse oximeter as mentioned above, simultaneously with heart rate. Oxygen saturation is not measured during the 6MWT due to motion artefact which results in unacceptably high failure rates of the devices [66].

#### Ten meter timed walk

Participants are requested to walk 10 meters at their own regular pace between 4 small traffic cones which are placed in the corners of a 10 by 1 meter rectangle. Their walk is filmed from behind by a digital video camera (Panasonic NV-GS330, Matsushita Electric Industrial Co., Ltd. Osaka, Japan) standing at least 8 meters behind the start on an 24.25 inch tripod (Vanguard MK-4). Time to walk 10 meters is measured by hand with a stopwatch to the nearest of 1/10 of a second and by video-analysis. By video-analysis also walking speed measured over 6 meters, i.e. without the 2 meters at start and 2 meters at finish to exclude starting hesitation and the slowing down at finish, step frequency, base width and step length will be analysed.

#### Figure of eight

The figure of eight is an applicable and reliable dynamic functional balance measure of mobility for people with various degrees of physical disability [70,71] and geriatric patients [72]. The figure of eight test requires continuous turning during gait with an emphasis on accuracy (avoid oversteps), speed (timed task) and switching of motor patterns during the cross-over from the clockwise to the counter-clockwise loop. Participants are timed while walking in a figure-8 trajectory. The figure-8 trajectory is marked with white paint on a dark green rubber carpet, each loop having an outer diameter of 165 centimeters (cm) and a step width of 15 cm. The time to walk two complete eight figures is measured with a stopwatch. The onset time is based on the first detectable movement of the participant following a "Go!" command from the observer. Any step taken outside the white line is noted. The fastest attempt of two trials is recorded together with the corresponding oversteps. Speed (m/s) is 19.792 meter divided by the time in seconds.

#### Timed up and go (TUG)

The TUG is a reliable and valid test for quantifying functional mobility that may also be useful in following clinical change over time [73]. To complete the TUG, participants are requested to rise from a standard chair (48 cm height, horizontal seat and armrests), walk 3 meters, turn around and return to a fully seated position in the chair again [74]. Each participant has two trials and the average time in seconds is the outcome of the TUG. Scores under 10 seconds are associated with individuals who are functionally independent in the frail elderly population [74].

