#### Sit to stand (STS)

The STS is normally a reliable and valid indicator of lower body strength in adults over the age of 60 years [75]. However, in this study participants are allowed to use upper limbs to rise from the chair to test their rising performance that is closest to the clinical setting and to reduce a floor effect; a high percentage of older dependent elderly cannot rise from a chair with the arms crossed in front of the chest [76,77]. Participants are instructed to stand up and sit down in a standard chair as many times as possible within 30 seconds. The STS score is formed by the total number of performances with a sit-stand-sit performance counting as 1. Ending in a standing position is counted by a 0.5 point.

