## Discussion

This paper presents the design of a RCT, which aims to explore the longitudinal effect of regular walking on several health aspects of older people with dementia. The strength of this study is that 1) the intervention is not performed by the research staff, but by the nursing staff which enables it to become a routine in usual care, 2) we have a high number of repeated measurements, i.e. one baseline and 6 post measurements, 3) the various outcome variables enables us to analyse the development of different health aspects within 18 months.

Possible limitations of this study are that 1) only active minded institutions are willing to participate creating a selection bias, 2) there will be a (high) drop-out rate, for example due to death, 3) not all participants will be able to perform/understand all tests.

This method is appropriate to collect data on the effectiveness and feasibility of a walking program. It is also interesting to examine what aspects determine the compliance of the participants. Due to the aging and dementia process, it is not always necessary to increase in test score to find an effect of the intervention, but stabilizing cognitive and behavioural functioning in those who participate in the walking group would also be worthwhile.

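### The TUG, ten-metre walk and figure-of-eight outcomes have no value for a participant who is assessed but physically unable to complete the walk

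*Protocol article*

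**What the plan says.** All places are in the Protocol article.

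- **Timed up and go (TUG):** "Each participant has two trials and the average time in seconds is the outcome of the TUG". No other TUG score is defined.
- **Ten meter timed walk:** "Time to walk 10 meters is measured by hand with a stopwatch to the nearest of 1/10 of a second and by video-analysis". There is more than a time: "By video-analysis also walking speed measured over 6 meters", together with step frequency, base width and step length.
- **Figure of eight:** "The time to walk two complete eight figures is measured with a stopwatch"; "The fastest attempt of two trials is recorded together with the corresponding oversteps"; "Speed (m/s) is 19.792 meter divided by the time in seconds".
- **Sit to stand (STS):** "The STS score is formed by the total number of performances". This is a count. The six minute walk test (6MWT) is scored as a distance and FICSIT-4 as summed seconds of standing. All three scales can take the value 0.
- **Participants and Procedure:** everyone is ambulatory at entry, walking aids are allowed, and the last measurement is at 18 months.
- **Discussion (and Abstract):** among the limitations, listed separately from drop-out, "not all participants will be able to perform/understand all tests".
- **Statistical analysis:** a repeated-measures comparison of the two groups. The section gives no score for a test that could not be performed.

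**The concern.** A participant with advancing dementia may attend a visit, be assessed, and no longer be able to rise and walk. The clinical result is then known: unable. The TUG outcome as defined does not exist for that person, since a time in seconds has no finite worst value. The ten-metre time, its video measures, and the figure-of-eight time, oversteps and speed do not exist either, because each needs a walk.

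This differs from death or withdrawal, where nothing is observed. Here the variable is empty because the outcome is bad. A repeated-measures model that tolerates incomplete data does not cure this, since absence depends on the very function being measured.

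Physical functioning is the first outcome named in the aim, and the Discussion says that stabilising function would be worthwhile. If regular walking keeps people mobile, more controls than walkers will lose the test, and the comparison among those still able will miss part of the effect sought.

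**Working it through.** **Plan's own figure.** The article gives no figure on this point: no inability rate and no mean or SD for any walking test. Its sample size (70 per group, Cohen's f = 0.32) rests on cognition and is not used here, except for the number left after attrition: 175 × 0.75 = 131.25, or about 65.5 per arm.

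**Step 1. Which measures survive inability?**

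| Test | Measures defined | Value if no walk is possible |
|---|---|---|
| TUG | mean seconds | none |
| Ten-metre walk | seconds, speed, step frequency, base width, step length | none stated |
| Figure of eight | seconds, oversteps, 19.792 m / time | none stated |
| 6MWT, STS, FICSIT-4 | metres, count, seconds held | scale can be 0; no rule stated |

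**Step 2. How much can the able-only difference shrink?** Assumptions, none from the article: latent walking speed is normal with mean 0.6 m/s and SD 0.2 in controls; the intervention shifts it by d = 0.5 SD (0.10 m/s); participants below a cut c are unable, with c set so that a share p of controls is unable.

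In SD units, the able-only means are
- control: φ(c) / (1 − Φ(c))
- intervention: d + φ(c − d) / (1 − Φ(c − d))

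For p = 10%, c = −1.2816:
- control: 0.1755 / 0.90 = 0.195
- intervention: c − d = −1.7816, so 3.7% are unable and the mean is 0.5 + 0.0816 / 0.9626 = 0.585
- difference: 0.585 − 0.195 = 0.390, and 0.390 / 0.5 = 78%

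| Controls unable | Intervention unable | Able-only difference / true |
|---|---|---|
| 2% | 0.5% | 93% |
| 5% | 1.6% | 86% |
| 10% | 3.7% | 78% |
| 20% | 9.0% | 66% |
| 30% | 15.3% | 56% |

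With d = 0.3 the ratios at 10, 20 and 30% are about 76, 63 and 54%.

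**Step 3. Power at one visit, 65.5 per arm, d = 0.5 (two-sample test).** Results at 10, 20 and 30% of controls unable:
- TUG seconds (6 m / speed), able only: 0.64, 0.55, 0.45
- speed with 0 for unable: 0.79, 0.77, 0.75

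Two things change between these lines. At 10%, able-only speed already reaches 0.69. So of the 0.15 gain, 0.69 − 0.64 = 0.05 comes from leaving seconds and 0.79 − 0.69 = 0.10 from keeping the unable.

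**Step 4. What zero-scoring does to the mean.** The mean with zeros is P(able) × (0.6 + 0.2 × able-only mean). At 10%:
- control: 0.90 × 0.639 = 0.575
- intervention: 0.9626 × 0.717 = 0.690
- difference: 0.115 m/s, or 115% of the latent 0.10

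At 20% and 30% it is 134% and 151%. The zero-scored mean difference therefore overstates the latent speed difference.

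**Step 5. A rank-based check.** Same structure with 70 per arm, fixing the share unable in both arms (assumed). For 20% against 10%, the true difference is 1.2816 − 0.8416 = 0.44. Able-only it is (0.44 + 0.195) − 0.350 = 0.285, a loss of 35%.

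| Unable, control / intervention | True difference (SD) | Able-only | Loss | Power, able only (t test) | Power, unable ranked worst (Mann-Whitney) |
|---|---|---|---|---|---|
| 10% / 5% | 0.36 | 0.28 | 24% | 44% | 56% |
| 20% / 10% | 0.44 | 0.29 | 35% | 48% | 71% |
| 30% / 15% | 0.51 | 0.29 | 43% | 50% | 82% |
| 30% / 20% | 0.32 | 0.17 | 46% | 21% | 42% |

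With 20% unable in both arms and no effect, both analyses reject about 5% of the time and the able-only difference is zero.

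**The case against.** The strongest case against is that this is ordinary missing-data handling. Rules for a test that cannot be performed often sit in an analysis plan or a test manual, and a journal article condenses both. That part stands: silence in the Statistical analysis section is not evidence that no rule exists. What remains is the outcome definition, which the article does fix. The TUG result is average seconds, and a general missing-data rule would treat a known inability as an unknown value.

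Two stronger readings are tempting, and the article supports neither. A reader might infer that all three tests are scored only as a time. That is true of the TUG alone; the other two also yield speed and gait measures or oversteps, although none is defined without a walk. A reader might also infer that a participant who cannot walk scores 0 on STS, 6MWT and FICSIT-4, so that one event is worst on three tests and missing on three. Those scales can take 0, but no section says inability is scored so. STS allows use of the arms and FICSIT-4 tests standing, so such a participant may score above 0 on both. The nearest contrast is 6MWT distance.

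It is also fair that every rate in the working is assumed, that regular walking aids are permitted in all the tests and may make inability uncommon, and that these are three among many outcomes.

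**Conclusion.** The point holds as a badly fixed outcome definition. For a participant who is assessed but physically unable, the TUG, ten-metre walk and figure-of-eight measures have no value, although the protocol foresees inability.

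The likely direction, if walking works, is an understated benefit and lower power. It is a conditional direction: it needs inability to differ between arms, and with no effect and equal loss the comparison is not biased. A reader might conclude that the trial will hide the decline it studies; without inability rates the article does not show that. At 2 to 5% of controls unable, the able-only difference keeps 93 to 86% of its true size, a modest loss. At 20 to 30% it keeps 66 to 56%, which is serious. These figures rest on a normal latent speed, a sharp cut-off and a 0.5 SD benefit. The change is worth making because it is cheap and because the reason for non-completion may not be recoverable after the visit.

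**What to change.** 1. On the test form, record at each visit why a timed walking test was not completed: physically unable, refused, did not understand, or absent.
2. Analyse the TUG as speed or 1/time, and the other two tests as speed.
3. Set physical inability to 0 or to the worst rank, and compare the groups with a rank-based method. Under ranks the two choices give the same result. Keep the other three reasons as missing.
4. Alongside, report times among completers and the proportion unable per arm, so that a reader can see how far the two diverge.

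**Cost.** One reason code on the form and a short scoring rule in the analysis plan, including how the rank comparison fits with the repeated-measures analysis. The distribution gains a spike at its floor. With zeros included, the mean difference no longer estimates the latent speed difference (115 to 151% of it in the working above), which is why the comparison should be by rank. TUG in seconds becomes descriptive.

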#### Sit to stand (STS)

The STS is normally a reliable and valid indicator of lower body strength in adults over the age of 60 years [75]. However, in this study participants are allowed to use upper limbs to rise from the chair to test their rising performance that is closest to the clinical setting and to reduce a floor effect; a high percentage of older dependent elderly cannot rise from a chair with the arms crossed in front of the chest [76,77]. Participants are instructed to stand up and sit down in a standard chair as many times as possible within 30 seconds. The STS score is formed by the total number of performances with a sit-stand-sit performance counting as 1. Ending in a standing position is counted by a 0.5 point.

#### Frailty and injuries: cooperative studies of intervention techniques (FICSIT-4)

The FICSIT-4 is a test to measure static balance [78]. The participants have to maintain balance in 4 positions with increasing difficulty. Each position is demonstrated first and support is offered while participants position their feet. When participants are ready, the support will be released and timing begins. The timing stops when participants move their feet or grasp the researcher for support, or when 10 seconds have elapsed. Only when one stand is performed 10 seconds, the next, more difficult stand is performed. The first stand is with the feet together in parallel (side-by-side) position. Second is the semi-tandem position; the heel of one foot is placed to the side of the first toe of the other foot. The participant can choose which foot to place forward. Third is a tandem position; the heel of one foot directly in front of the toes of the other foot. The final stand is standing on one leg. The total summed seconds of all stands is the outcome score.

### Assessment of cognition

Cognition will be assessed by the following neuropsychological tests:

#### Mini-Mental State Examination (MMSE)

The MMSE measures the global level of cognitive functioning [79]. Globally, a score between 25 to 30 indicates no dementia, between 15-24 mild dementia, between 5-14 moderate to severe dementia and between 0 to 4 profound dementia [80].

#### Eight words test

The eight words test is a list learning test for people with memory problems [81]. In this test the examiner reads out eight words in a row, which is repeated five times. Every time the participant is asked to recall as many words as possible. The first outcome measure is the total number of correctly recalled words after the five trials (*immediate recall score*, maximal score = 40). After an interval of approximately 15 minutes the participant is asked to recall as many words as possible (*delayed recall score*, maximal score = 8). Subsequently, the examiner reads aloud 16 words among which 8 words presented before and 8 new words. The participant is asked to recognize the words from the list presented before (*recognition score*, maximal score = 16).

#### Rule shift cards

The rule shift cards is a subtest of the Behavioural Assessment of the dysexecutive Syndrome (BADS) [82]. This subtest purports mental flexibility and is one of the best qualifiers to discriminate people with perseverative tendency, i.e. an executive dysfunction, from healthy people [83]. Participants have to respond to stimuli (red or black playing cards) according to one of two rules that are presented consecutively. Performance is scored according to how successfully the respondent shifts from applying the first to the second rule [82].

#### Key search

The key search test is also a subtest of the BADS [82] and is used to measure how well the participant is able to prepare an efficient plan of action in the context of a routine event [83]. The patient is asked to imagine that a 100-mm square on an A4 size paper is a large field, in which they have lost their keys. They are asked to draw a line, beginning at a black dot, 50 mm below the square, to show the strategy they would use to search the field, to make absolutely certain that they would find their keys. The test evaluates a person's ability to monitor and evaluate their own performance, taking into account factors that are not explicitly stated in the instructions. Their search strategy score is based on a number of criteria, such as efficiency and effectiveness. The best strategy score is 15 and the worst score is 2.

#### Digit span (forward and backward)

The digit span is a subtest from the Wechsler Memory Scale-Revised (WMS-R) [84]. In the digit span forward, increasingly long sequences of random numbers are orally presented at a rate of one digit per second to the participants, who have to repeat the sequence immediately after oral representation. In the digit span backward, participants have to repeat the sequence in reverse order. To do this, participants perform extra mental operations on the information that is being held in short term memory. While the backward condition is often hypothesized as tapping more into EF than the forward condition which should measure more short term memory, research has failed to demonstrate this result [85,86]. These studies suggest that both conditions tap into EF. Each condition ends when a participant fails to recall at least two strings of the same length or repeated an eight-digit sequence correctly. The minimal score for both conditions is 0 and the best score is 21.

